#### Control

Participants randomized to the control arm are advised to seek referral to usual care CR—as described above—if they wish to participate. No additional support is provided (Figure 1).

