#### Process Evaluation

Semistructured exit interviews are conducted to understand usability, acceptability, engagement, and satisfaction with the SCRAM and usual care CR treatments, respectively. SCRAM treatment fidelity is assessed via exercise session completion (determined from recorded exercise training data), self-reported compliance with behavioral notifications, and SCRAM platform usage metrics. Usual care treatment fidelity is assessed via self-reported uptake of standard CR services. Process data will be summarized using descriptive statistics (quantitative questions and analytics) and general inductive thematic analyses (open-ended questions). Interview data will be transcribed verbatim and analyzed using a general inductive thematic approach [52].

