#### Statistical Analysis

Baseline characteristics will be summarized descriptively for the full sample and by treatment group. A linear regression model—adjusted for baseline values and stratification variables—will be fitted to assess the primary outcome. Primary analyses will be performed on the principle of intention to treat. Assuming there is a reasonable amount (>5%) of missing data, primary analyses will be conducted using multiple imputation, imputing all outcomes using a single (joint) imputation model. Imputation models will include participant age, sex, type of diagnosis (eg, angina, myocardial infarction, and coronary revascularization), in addition to any other covariates that appear to predict missingness. A per-protocol analysis will be conducted with complete cases to test the robustness of treatment effects under different assumptions. Preplanned subgroup analyses will be conducted to determine treatment effects by levels of treatment adherence, sex, and trial center (Figure 1). Secondary analyses will adjust the regression model for baseline prognostic factors, including age, sex, and employment status.

A similar approach will be used to assess continuous secondary outcomes (Table 3); logistic regression will be used for binary outcomes. Model-adjusted estimates and group differences will be reported with 95% CIs and probability values. All statistical tests will be 2-sided at α=.05. The biostatistician will remain blinded throughout the analysis of treatment effects. A detailed statistical analysis plan will be developed before the completion of data collection to guide analyses.

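### Treatment adherence, which arises after randomisation and has no equivalent measure in the two arms, is listed beside sex and trial center as a subgroup factor for treatment effects

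*Protocol article*

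**What the plan says.** The subgroup sentence in Statistical Analysis reads: "Preplanned subgroup analyses will be conducted to determine treatment effects by levels of treatment adherence, sex, and trial center". It gives the three factors equal standing and does not mark adherence as exploratory. Under Randomization, sex and trial center are the stratification variables.

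Process Evaluation describes how engagement is measured in each arm. For the intervention, "SCRAM treatment fidelity is assessed via exercise session completion (determined from recorded exercise training data"; the same sentence adds self-reported compliance with the notifications and platform usage metrics. For the comparator, "Usual care treatment fidelity is assessed via self-reported uptake of standard CR services".

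The Control section sets no behaviour to adhere to: controls "are advised to seek referral to usual care CR", should they want to take part, and "No additional support is provided". The Intervention section leaves usual care CR open to the SCRAM arm as well.

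On the main analysis, Statistical Analysis says: "Primary analyses will be performed on the principle of intention to treat". It adds multiple imputation when more than 5% of data are missing. A separate sentence says: "A per-protocol analysis will be conducted with complete cases to test the robustness of treatment effects under different assumptions".

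**The concern.** A subgroup effect is protected by randomisation when membership is fixed before allocation, so that each stratum holds a randomised SCRAM group and a randomised control group. Adherence fails this test in two ways. It is observed after allocation, and the variable that places a SCRAM participant in the high stratum (recorded sessions, notifications, platform use) is not observed for a control. A control who never attends CR has not departed from the assignment, and CR attendance is open to both arms, so it does not identify the controls who would have adhered to SCRAM.

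Any contrast by adherence level therefore sets a self-selected part of SCRAM against either all controls or a differently selected part of them. The outcome is fitness and the main adherence measure is completed exercise sessions, so it is plausible that people likely to do well for other reasons also complete more sessions. The result could then look like a dose-response gradient when the effect is the same for everyone, and readers could take it as support for efficacy.

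**Working it through.** **Inputs from the Sample Size section.** Target difference 2.0 mL/kg/min, SD 6.75, correlation between repeated measures 0.80, power 0.90, two-sided alpha 0.05, 174 evaluable, 220 in total.

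**Reproducing the plan's figure.** SD after baseline adjustment: 6.75 × √(1 − 0.80²) = 6.75 × 0.6 = 4.05. Per arm: 2 × (1.960 + 1.282)² × 4.05² / 2.0² ≈ 86.2, rounded up to 87, so 2 × 87 = 174, as stated. Dividing by 0.80 for loss to follow-up gives 217.5, or 218, against 220 stated. The value 4.05 is thus the residual SD that the plan itself implies.

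**Assumptions not in the article.** Let ρ be the correlation between a participant's tendency to adhere (taken as normal) and the 24-week outcome given baseline. Let SCRAM be split at median adherence, and let each half be compared with all controls. The true effect is 2.0 in everyone.

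**Shift in each half.** ρ × 4.05 × φ(0)/0.5 = ρ × 4.05 × 0.798 = ρ × 3.23.

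| ρ | Shift | High-adherence half | Low-adherence half |
|---|---|---|---|
| 0 | 0 | 2.00 | 2.00 |
| 0.1 | 0.32 | 2.32 | 1.68 |
| 0.2 | 0.65 | 2.65 | 1.35 |
| 0.3 | 0.97 | 2.97 | 1.03 |

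**Check by simulation.** 87 per arm, baseline-adjusted linear model, 3,000 runs per setting.

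- *True effect 2.0:* the halves averaged 2.31 and 1.65 at ρ = 0.1, and 2.97 and 1.03 at ρ = 0.3, in line with the formula.
- *True effect 0:* the high-adherence half differed from all controls by 0.31, 0.64 and 0.96 at ρ = 0.1, 0.2 and 0.3. The two-sided 5% test rejected in 7%, 13% and 25% of runs. The low-adherence half showed the mirror image (−0.35, −0.65, −0.98).
- *Another control group:* comparing high adherers with the controls who take up CR (assumed 30%, uptake assumed unrelated to prognosis) left the same bias, 0.96 at ρ = 0.3. If control uptake were itself prognostic, size and direction would depend on both selections, and nothing in the article makes them cancel.
- *Benchmark:* a factor equivalent to a baseline trait and measured identically in both arms gave no bias with no true effect (estimates −0.03 to 0.01, rejection 5% to 6%). The trouble therefore comes from the missing counterpart in controls, not from subgrouping as such.

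**The case against.** Several points on the other side are sound.

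- *The analysis is secondary.* The primary analysis follows intention to treat, and nothing in the article says that the adherence subgroup will carry an efficacy claim. This stands and limits the severity.
- *Detail is deferred.* A statistical analysis plan is announced, and the subgroup sentence points to Figure 1, which is not shown. Either may define adherence levels. However, a definition supplies cut-points, not a control counterpart; the later plan could cure the problem only by departing from the analysis stated here.
- *The size rests on assumptions.* The correlation and the median split are not in the article. At ρ = 0 there is no bias, and at ρ = 0.1 the false-positive rate is 7% against a nominal 5%. This stands, so the claim is that the analysis can mislead, not that it must.

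Two stronger readings are tempting and are not supported. A reader might infer that adherence is observed only in SCRAM; the article also collects self-reported CR uptake for usual care, so the accurate statement is that the measures are not equivalent.

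A reader might also infer that the per-protocol analysis drops poor adherers from SCRAM alone and so favours SCRAM. Removing the least adherent 30%, for instance, would add 0.20 to 0.60 for ρ of 0.1 to 0.3. But the article gives no adherence rule for that set, whose definition may properly sit in the analysis plan. Complete-case status depends on observed outcomes, which can be missing in either arm. If SCRAM participants who also attend CR were excluded, the estimate could fall.

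**Conclusion.** The point holds for the adherence subgroup. A post-randomisation variable with no common scale across arms, and no required behaviour in controls, is preplanned as though it were a baseline factor, so the resulting stratum effects are not protected by randomisation. With a uniform true effect of 2.0, the apparent gap between the two halves would run from 0.64 (2.32 − 1.68) at ρ = 0.1 to 1.94 (2.97 − 1.03) at ρ = 0.3, the latter nearly as large as the target difference. These figures rest on the assumed ρ, a median split and all controls as comparator; they vanish at ρ = 0.

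It does not follow that the trial's treatment effect is invalid: the primary analysis and the 174/220 sample size are unaffected. Nor is the per-protocol analysis shown to be biased. Its only visible weakness is that it may change the population and the missing-data handling together, so that a difference from the imputed intention-to-treat result could not be traced to either. Agreement would still be informative, and this is a secondary remark, not a demonstrated error. The change should be made, but it is not critical.

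**What to change.** 1. Limit the formal subgroup analyses to sex and trial center, each with a treatment-by-subgroup interaction test, and remove adherence from that list.
2. Report associations between adherence and outcome within SCRAM only, labelled descriptive and exploratory.
3. Optionally, add a complier-average causal effect with randomisation as instrument and the same baseline and stratification adjustment. Define the exposure as engagement with any SCRAM component (sessions, notifications, calls). Session completion alone is too narrow, because notifications and the weekly maintenance-phase calls can act outside it. State the exclusion restriction: allocation affects VO2max only through that engagement. A change in usual care CR uptake caused by allocation would also breach it.
4. As a secondary improvement, add an intention-to-treat complete-case analysis, so that the effect of missing-data handling can be separated from that of the per-protocol population.

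The cost is a change of wording and a little analysis work; no sample size or data collection changes. The complier effect has a wider interval and rests on an untestable assumption. With an exposure this broad it may also lie close to the intention-to-treat estimate if nearly everyone engages.

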#### Sample Size

Our previous noninferiority trial [10] indicates that 174 participants are required to detect a clinically meaningful between-group difference of 2.0 mL**·**kg^−1^**·**min^−1^ in VO_2_max (SD 6.75 mL**·**kg^−1^**·**min^−1^, r=0.80 between repeated measures, β=.9, and 2-sided α=.05). Allowing for 20% loss to follow-up (17% in our previous trial), a total of 220 participants are required to ensure equal numbers per treatment arm (ie, 110 per arm). Minimum detectable between-group differences in secondary outcomes at 24-week follow-up are summarized in Table 4.

**Table 4 table4:** Minimum detectable differences in secondary outcomes (assuming a total sample size of 220 participants [110 per treatment arm] and beta=.8).

Secondary outcome	Group difference	Data source
Total cholesterol concentration	0.24 mmol·L^−1^	Maddison et al [10]
Low-density lipoprotein cholesterol concentration	0.16 mmol·L^−1^	Maddison et al [10]
High-density lipoprotein cholesterol concentration	0.10 mmol·L^−1^	Maddison et al [10]
Triglyceride concentration	0.29 mmol·L^−1^	Maddison et al [10]
Glucose concentration	0.60 mmol·L^−1^	Maddison et al [10]
Physical activity leisure score index	17%	Dale et al [40]
Health-related quality of life	0.06 units	Richardson et al [56]
Medication adherence	19%	Thornley et al [57]
Systolic blood pressure	4.70 mmHg	Maddison et al [10]
Diastolic blood pressure	2.76 mmHg	Maddison et al [10]
Body mass	3.80 kg	Maddison et al [10]
Body mass Index	0.90 kg/m^2^	Maddison et al [10]
Waist circumference	2.60 cm	Maddison et al [10]
Hip circumference	1.80 cm	Maddison et al [10]
Alcohol consumption	21%	Dale et al [40]
Dietary guideline index	3.70 units	Livingstone and McNaughton [45]

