### Randomization

Upon completion of baseline data collection, participants are randomized at a 1:1 ratio to receive 24 weeks of usual care CR alone (control) or the 24-week SCRAM program (intervention). Treatment allocation follows a computer-generated schedule prepared by a biostatistician who is not involved in recruitment, treatment allocation, or outcome assessment; the randomization schedule is stratified by sex and trial center and uses random permuted blocks (n=2 and 4). A centralized Web-based randomization system (Research Electronic Data Capture [REDCap]; Vanderbilt University) ensures allocation concealment until the time of randomization. Access to the randomization schedule is restricted to the blinded trial biostatistician. The trial steering group is permitted access to summarized allocation progress data to monitor recruitment. Researchers undertaking data collection have no access to the randomization schedule other than to retrieve participants’ concealed treatment allocation at baseline assessments.

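### Table 4 states 24-week detectable differences on all 220 randomised participants despite the planned 20% loss, and its 21% alcohol entry cannot arise under the table's own heading

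*Protocol article*

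**What the plan says.** All of the following is in the protocol article.

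- **Sample Size, primary outcome:** "174 participants are required to detect a clinically meaningful between-group difference of 2.0" mL/kg/min in VO2max, with SD 6.75, a correlation of 0.80 between repeated measures, 90% power and two-sided 0.05. Then: "Allowing for 20% loss to follow-up (17% in our previous trial), a total of 220 participants are required".
- **Sample Size, secondary outcomes:** "Minimum detectable between-group differences in secondary outcomes at 24-week follow-up are summarized in Table 4". The table heading reads "Minimum detectable differences in secondary outcomes (assuming a total sample size of 220 participants [110 per treatment arm] and beta=.8". No SDs, correlations or control proportions are shown.
- **Table 4 entries used here:** systolic pressure 4.70 mmHg, LDL cholesterol 0.16 mmol/L, waist 2.60 cm, body mass 3.80 kg, BMI 0.90 kg/m², physical activity 17%, medication adherence 19%, alcohol 21%.
- **Table 3:** alcohol, medication adherence and physical activity are each defined as a percentage meeting a threshold, so they are binary. Lipids, glucose, blood pressure and anthropometry are measured at baseline and week 24 only. The questionnaire and diet outcomes are also collected at week 12.
- **Statistical Analysis:** "All statistical tests will be 2-sided at α=.05". With more than 5% missing data, all outcomes are imputed jointly.
- **Randomization:** "participants are randomized at a 1:1 ratio".

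**The concern.** One paragraph makes two assumptions about the same visit. For the primary outcome, a fifth of participants are expected to be lost by week 24, and recruitment is raised to compensate. For the secondary outcomes at that visit, nobody is lost.

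The table also does not appear to follow its own heading throughout. For a binary outcome the detectable difference has a ceiling that depends only on sample size, power and significance level, because the binomial variance is greatest near 50%. An entry above the ceiling cannot have come from the stated inputs.

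Table 4 is the article's only statement of what the trial can detect on its secondary outcomes, and the Objectives hypothesise superiority on those outcomes too. A reader who takes the table at face value would credit the trial with more sensitivity than it may have when interpreting a null secondary result.

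**Working it through.** **Inputs.** Table 4: 110 per arm and 80% power. It is printed as beta=.8 and read here as power, as the primary calculation's β=.9 must be. Alpha is two-sided 0.05 (Statistical Analysis), allocation 1:1 (Randomization) and loss 20% (Sample Size). Normal quantiles: 1.960 (alpha), 0.842 (80% power), 1.282 (90% power).

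**Step 1. Reproduce the primary calculation.** With baseline adjustment, n per arm = 2 × (1.960 + 1.282)² × SD² × (1 − r²) / difference² = 2 × 10.51 × 45.56 × 0.36 / 4 = 86.2, so 87 per arm and 174 in total. Then 174 / 0.8 = 217.5, so 218, against the stated 220. The figure reproduces and is a number of completers. The number expected at week 24 is 220 × 0.8 = 176, or 88 per arm.

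**Step 2. Continuous rows, if computed at 220.** The detectable difference is proportional to 1/√n, so moving from 220 to 176 multiplies it by √(220/176) = 1.118.

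| Row | As printed | At 176 |
|---|---|---|
| Systolic pressure (mmHg) | 4.70 | 5.25 |
| LDL cholesterol (mmol/L) | 0.16 | 0.18 |
| Waist (cm) | 2.60 | 2.91 |

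Power at the printed difference is Φ(2.802 × √0.8 − 1.960) = Φ(0.546) = 0.707. With the previous trial's 17% loss instead, it is Φ(2.802 × √0.83 − 1.960) = Φ(0.592) = 0.72, and the factor is 1/√0.83 = 1.098.

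**Step 3. Binary rows.** No control proportion is given, so every control rate was scanned and the largest detectable difference d taken. The pooled formula is n per arm = [1.960 × √(2p̄(1 − p̄)) + 0.842 × √(p1(1 − p1) + p2(1 − p2))]² / d². The maximum lies where the two rates straddle 50%.

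| Basis | Largest d, pooled | With continuity correction |
|---|---|---|
| 110 per arm, 80% power (as headed) | 18.8 points | 19.7 points |
| 88 per arm, 80% power | 21.0 points | 22.1 points |
| 110 per arm, 90% power | about 21.7 points | 22.5 points |

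Other methods at 110 per arm and 80% power give 18.6 (unpooled), 18.8 (arcsine) and about 19.7 (Fisher exact, rates centred at or near 50%).

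- **Alcohol, 21%:** above the ceiling under every method. At 110 per arm a 21-point difference has at least (0.21 × √110 − 1.386) / 0.691 = 1.18, that is 88.1% power (85.3% by Fisher). At 88 per arm, worst-case power is 80.1%.
- **Medication adherence, 19%:** obtainable; 18.8 rounds to 19.
- **Physical activity, 17%:** obtainable, for example from a control rate of 20%.

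**Step 4. Body mass against BMI.** 3.80 / 0.90 = 4.22 m², a height of 2.05 m if both entries described the same weight change in one person. They need not. Each is a multiple of its own outcome's SD, and the SD of weight also carries variation in height. Under assumed values (mean height 1.72 m, height SD 7–10 cm, mean BMI 28.5, BMI SD 3.5–5 kg/m²) the ratio of SDs is 3.3–4.1 m². Slightly different correlations for the two outcomes could bring the ratio of detectable differences to 4.22.

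**The case against.** The heading states its N openly, and joint multiple imputation keeps all 220 in the analysis. That stands as far as it goes. Disclosure does not reconcile the figure with the loss assumed just before it, however, and the authors did not rely on imputation for the primary outcome. For the 11 rows measured in person (four lipid, one glucose, two blood pressure, four anthropometric) there is no week-12 value from which to recover a missing week-24 one, so imputation cannot be counted on to restore the lost information.

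The objection is stronger for the other five rows. Physical activity, diet, alcohol, medication adherence and quality of life are also collected at week 12. The Outcomes section allows self-report by telephone or internet from those who cannot attend at week 24. Retention may exceed 80% there, so applying 20% loss to every row would be an assumption.

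A reader might infer that the whole table has 71% power. The document does not support this: without SDs no continuous row can be tied to 110 or to 88 per arm, and the alcohol row casts doubt on the heading itself. If 110 per arm is right, the alcohol entry errs on the cautious side.

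A reader might also infer that the body mass or BMI entry is impossible, or wrong by a calculable percentage. Baseline-adjusted models hold a person's height essentially fixed, so the ratio does look odd, but the underlying SDs and correlations are not shown.

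Finally, Table 4 drives no design decision, and results will be reported with 95% confidence intervals. That limits the consequence but does not make the table right.

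**Conclusion.** The point holds in two parts.

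1. Table 4's 24-week differences rest on the number randomised, while the same paragraph expects about 176 with data. For any continuous row actually computed at 220, power at the printed difference is about 71% rather than 80%, or the 80%-power difference is about 12% larger. This is conditional on the heading being accurate and on 20% loss for that outcome; it bears chiefly on the in-person measures.
2. One entry, and only one, contradicts the heading. The 21% for alcohol cannot be obtained at 110 per arm, 80% power and two-sided 0.05 for any control rate, provided that it is an absolute difference in proportions. It is tempting to conclude that the row was computed at 88 per arm. It fits that, but it also fits 110 per arm at 90% power, so the source of the discrepancy cannot be identified.

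The body mass and BMI pair is an anomaly to check, not a demonstrated error. The primary sample size of 174, raised to 220, is sound on its stated inputs.

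**What to change.** Recompute Table 4 on one stated basis: 80% power, two-sided 0.05, about 176 analysed (88 per arm). If better retention is expected for outcomes that can be collected by telephone or internet, state that rate and use it for those rows only. Correct the alcohol row, or explain it by saying whether 21% is an absolute difference and which control proportion it assumes. Check the body mass and BMI entries against their source SDs and correlations. Restate the heading to match, giving 80% as power rather than as beta.

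The cost is a recalculation and a table correction. Some stated differences will become slightly less favourable. Recruitment, the primary analysis and trial conduct do not change.

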### Protocol Amendments

The medication adherence self-report instrument was changed to the 4-item Morisky, Green, and Levine Medication Adherence Scale [48]—before prospective clinical trial registration—to comply with trademark restrictions on the 8-item Morisky Medication Adherence Scale.

Amendments will be formally documented in the version-controlled trial protocol. Changes will be disseminated to the approving ethics committees and participants as required, and the trial registration will be updated as required.

### Availability of Data

Following trial completion and publication, requests for deidentified individual participant data or trial documents will be considered where the proposed use complies with trial ethical approval, does not conflict with planned use by the trial steering committee or other external data requests, and aligns with public good purposes, as well as where the requestor is willing to sign a data access agreement.

